## Abstract

Introduction: Osteoporosis is a major public health concern among postmenopausal women, characterized by decreased bone mineral density and microarchitectural deterioration, which lead to fragility fractures, pain, functional impairment, sleep disturbances, and a reduced quality of life. Exercise, particularly strength, weight-bearing, and balance training, represents a key non-pharmacological approach to prevention and management. Pilates, a low-impact, core-centered method increasingly incorporated into rehabilitation settings, appears especially suitable for women with osteoporosis. However, high-quality randomized controlled trials concurrently evaluating its effects on pain, balance, sleep, autonomy, and health-related quality of life remain scarce. Objective: To examine the efficacy and feasibility of a Pilates-based exercise program in improving pain, balance, sleep quality, functional autonomy, and quality of life in postmenopausal women with osteoporosis. Methods: A single-blind, parallel-group, randomized controlled trial will be conducted over 12 weeks at Physiocare Madrid (Spain). A total of 126 (63 per group) postmenopausal women aged 50–80 years, diagnosed with osteoporosis by densitometry or with a prior fragility fracture, will be randomly assigned (1:1; OxMaR software, version 2014) to one of two groups: (a) Experimental group: supervised Pilates mat sessions, 60 min, twice weekly for 12 weeks; or (b) Control group: ergonomics education for activities of daily living, two 60 min sessions held six weeks apart. Outcome assessors will remain blinded to group allocation. Evaluations will be conducted at baseline and post-intervention. Outcome measures will include balance and mobility (Timed Up and Go Test; Functional Reach Test), functional autonomy (Functional Independence Measure), pain intensity (Visual Analog Scale), sleep quality (Pittsburgh Sleep Quality Index), health-related quality of life (WHOQOL-BREF; QUALEFFO-41), and treatment satisfaction (CSQ-8). Feasibility parameters (recruitment, adherence, retention, and safety) will also be monitored. Data will be pseudonymized and analyzed descriptively to estimate variability and preliminary effects, informing the design of a definitive trial. Expected Results: It is hypothesized that Pilates will produce clinically meaningful improvements in balance, pain, sleep quality, and health-related quality of life compared with ergonomics education, with acceptable feasibility and safety outcomes. Conclusions: This randomized controlled trial will provide initial evidence regarding the efficacy and feasibility of Pilates as a complementary rehabilitation strategy for women with osteoporosis and provide key parameters to optimizing a future adequately powered trial. Ethics and Dissemination: This study will be conducted in accordance with the principles of the Declaration of Helsinki and has been approved by the Human Ethics Committee of Universidad Rey Juan Carlos. Potential risks will be minimized, and any adverse events will be systematically recorded and addressed.

## 1. Introduction

Osteoporosis is a systemic skeletal disorder characterized by reduced bone mineral density and deterioration of bone microarchitecture, resulting in increased bone fragility and a heightened risk of fractures even after minimal trauma. It constitutes a major global public health issue, particularly affecting postmenopausal women. Worldwide, approximately 200 million women are estimated to suffer from osteoporosis, with prevalence rising sharply with age. Nearly one in three women over 50 years of age will experience at least one fragility fracture during their lifetime [1]. In Spain, recent data indicate that approximately 18.6% of women over 50 years of age have osteoporosis, compared with 2.6% of men, and this figure increases to nearly 25% among women aged 65 years or older [2].

A particularly concerning feature of osteoporosis is its “silent” nature. Bone loss progresses asymptomatically until a fracture occurs, leading to frequent underdiagnosis and undertreatment [2]. Many patients remain unaware of their personal risk or fail to recognize the condition until after their first fragility fracture, causing delays in diagnosis and management [1]. Consequently, a substantial proportion of women do not receive timely preventive or therapeutic interventions [3].

The most direct clinical consequence of osteoporosis is the occurrence of fragility fractures, most commonly affecting the hip, vertebral column, wrist, and shoulder. These fractures cause acute pain and may lead to severe complications. Collectively, osteoporotic fractures have a profound impact on patients’ health, resulting in chronic pain, reduced quality of life, and increased hospitalization and disability rates [3,4]. Among these, hip fractures are of particular concern due to their high morbidity and mortality within the first year following the event, as well as the frequent loss of functional independence. Many patients are unable to regain their previous ability to walk or live independently.

Vertebral fractures may also lead to structural deformities such as thoracic kyphosis (osteoporotic hump) and postural alterations that disrupt body biomechanics. These deformities are often associated with chronic back pain and restricted trunk mobility [5,6]. Even in the absence of new fractures, established osteoporosis may cause trabecular microfractures—especially in vertebrae—that produce persistent pain and stiffness, further limiting physical activity [3,4,5,6]. Consequently, osteoporosis contributes to significant functional impairments, including decreased muscle strength, impaired balance, and reduced ability to perform daily activities, thereby increasing dependence on others for basic self-care [4,6]. Several studies have demonstrated that the decline in physical function and mobility associated with osteoporosis is comparable to that observed in other disabling chronic diseases [7].

Another critical aspect of osteoporosis is the increased risk of falls. Bone fragility heightens the likelihood of sustaining fractures after minimal trauma; thus, even a fall from standing height can result in serious injury. Among older adults in the general population, approximately 30–35% experience at least one fall each year, with a higher incidence in women due to factors such as sarcopenia and age-related impairments in balance and postural control [4,6]. In individuals with osteoporosis, these falls represent the leading cause of fragility fractures. This situation creates a vicious cycle: age-related declines in muscle mass and strength, coupled with neuromuscular deterioration, predispose individuals to falls; in the presence of fragile osteoporotic bone, such falls are more likely to cause fractures, which in turn exacerbate immobility and muscular weakness.

Beyond its physical consequences, osteoporosis exerts profound psychosocial and quality-of-life impacts. Functional limitations and chronic pain resulting from fractures, or from bone fragility itself, can negatively influence mood, confidence, and self-esteem. Even in the absence of fractures, many women with osteoporosis experience a persistent fear of falling or sustaining injury—often referred to as kinesiophobia or fear of movement—which leads to self-imposed reductions in physical activity [7,8]. Paradoxically, this sedentary behavior accelerates muscle loss and worsens balance impairments, further increasing the risk of falls.

Chronic pain also interferes with emotional well-being. Persistent discomfort and functional restrictions are often associated with anxiety and depressive symptoms. Consequently, osteoporosis not only causes pain and limits mobility but also contributes to social isolation and diminished self-esteem [4,6,7,8]. A study conducted among postmenopausal women with osteoporosis but without prior fractures reported that 58% presented symptoms of depression and 55% experienced chronic pain, along with significantly lower scores for quality of life and self-esteem compared with women without osteoporosis [9,10]. These findings highlight that the psychological burden of osteoporosis may arise even before fractures occur, substantially affecting emotional well-being and overall quality of life [4,9].

It is also important to emphasize the complex interplay between pain, sleep disturbances, and mood disorders in women with osteoporosis. Chronic osteoporotic pain—such as low back pain caused by vertebral compression fractures—often disrupts sleep, leading to insomnia or non-restorative sleep patterns. In turn, sleep deprivation heightens pain perception and contributes to daytime fatigue and irritability. Reciprocal relationships among poor sleep quality, pain, and depressive symptoms have been consistently observed in postmenopausal women with osteoporosis, where each factor exacerbates the others in a self-reinforcing cycle [4,5,6].

Sleep disturbances not only impair quality of life but may also increase the risk of falls due to drowsiness, reduced attention, and impaired gait stability. Consequently, osteoporosis involves multidimensional clinical consequences—physical (fractures, pain, disability), psychological (fear, depression, anxiety), and social (isolation, dependence)—that collectively impair health-related quality of life in affected women [4,5,6].

The management of osteoporosis generally includes pharmacological treatment with antiresorptive and anabolic agents, complemented by calcium and vitamin D supplementation [4]. Nevertheless, physical exercise is widely recognized as a cornerstone of both prevention and rehabilitation. Regular exercise contributes to attenuating bone loss, enhancing muscular strength, and improving postural control [8,10,11]. In particular, strength training, weight-bearing activities, and balance exercises are strongly recommended to reduce the risk of falls and promote greater functional independence [8,10,11].

The Pilates Method, developed by Joseph Pilates in the 1920s, focuses on achieving precise control of body position and movement [12]. It consists of a series of mind–body exercises designed to strengthen, stabilize, and increase flexibility of the body’s center or “core,” while emphasizing muscular control, postural alignment, and conscious breathing [13]. The method encompasses 33 exercises structured around seven fundamental principles: concentration, breathing, control, flow of movement, centering, and precision [12,13].

Although initially conceived as a form of physical exercise, the Pilates Method has increasingly been incorporated into rehabilitation programs aimed at reducing pain and disability, particularly in patients with musculoskeletal and rheumatologic conditions [14,15]. Its low-impact nature makes it especially suitable for women with osteoporosis, as it minimizes high-risk movements such as deep spinal flexion. Preliminary studies have demonstrated that Pilates can improve muscle strength, balance, pain, and overall quality of life in postmenopausal women with osteoporosis [11,16,17]. Furthermore, additional benefits have been observed in sleep quality, anxiety, and depressive symptoms [9].

Despite these promising findings, the current body of evidence remains limited. Most existing studies are constrained by small sample sizes, short intervention periods, and methodological heterogeneity [11,17]. To date, few high-quality randomized controlled trials have simultaneously assessed multiple clinically relevant outcomes, such as quality of life, pain, balance, sleep, and functional performance. Therefore, there is a clear need for a well-designed randomized controlled trial (RCT) to comprehensively evaluate the efficacy and feasibility of the Pilates Method in women with osteoporosis.

## 2. Materials and Methods

### 2.1. Study Design

A single-blind, RCT with a three-month intervention period will be conducted at Physiocare Madrid, located in the Autonomous Community of Madrid, Spain.

The development of this study protocol followed the SPIRIT 2025 guidelines [18]. This study will be prospectively registered at ClinicalTrials.gov and conducted in accordance with the CONSORT 2010 guidelines to ensure transparent and accurate reporting of its methodology and outcomes [19].

### 2.2. Sample Description

Participants receiving treatment at Physiocare Madrid will be invited to participate in this study. Recruitment will be conducted through informational posters displayed in various areas of the center and through an informational session specifically addressed to potential participants.

The inclusion criteria will be postmenopausal women (≥12 months of amenorrhea) aged 50–80 years; a documented diagnosis of osteoporosis confirmed by bone densitometry (T-score ≤ −2.5 at the lumbar spine, total hip, or femoral neck), or a history of medically or radiologically confirmed fragility fracture; absence of associated metabolic disorders such as Crohn’s disease; availability to attend two sessions per week for 12 consecutive weeks; and voluntary participation with the provision of written informed consent.

The exclusion criteria will include any medical contraindication to physical exercise; current participation in another similar intervention program during the same period; or refusal to participate voluntarily and/or failure to provide written informed consent.

Pharmacological treatment related to osteoporosis (including bisphosphonates, denosumab, teriparatide, or calcium and vitamin D supplementation) will not constitute an exclusion criterion, provided that the treatment has remained stable for at least three months prior to enrollment. All pharmacological treatments will be recorded as part of each participant’s clinical profile and considered as potential confounding variables during statistical analysis.

### 2.3. Procedure

Individuals meeting the inclusion criteria will be invited to voluntarily participate in this study. They will receive detailed information about the intervention, study procedures, potential risks, and expected benefits, enabling them to make an informed decision regarding participation. Those who agree to take part will be required to sign a written informed consent form (see Supplementary File S1).

Following the provision of informed consent, sociodemographic data will be collected, including name, age, sex, and any ongoing conventional therapies. Upon enrollment, each participant will be pseudonymized through the assignment of a unique alphanumeric identifier composed of the letter “P” followed by a sequential number corresponding to the order of inclusion (e.g., P01, P02, P03, etc.). These codes will be used in all study documentation and databases to ensure confidentiality and protect participant identity. The correspondence between the assigned codes and personal identifiers will be recorded in a secure file accessible exclusively to the principal investigator (PI).

All personal data obtained through informed consent will be processed in compliance with the European Union General Data Protection Regulation (EU Regulation 679/2016). Data will be stored in a secure research database accessible only to the study investigators.

All data collected during baseline and follow-up assessments will be entered into a Microsoft Excel database and subsequently exported to IBM SPSS Statistics (version 27) for analysis. Descriptive statistics (means, standard deviations, and frequency distributions) will be computed to characterize the sample and summarize the main study variables. Inferential analyses will be conducted to examine between-group and within-subject differences over time, using repeated-measures ANOVA or ANCOVA when appropriate, with baseline values included as covariates. Effect sizes and 95% confidence intervals will be reported to estimate the magnitude and precision of the observed effects. All statistical tests will be two-tailed, with the significance level set at *p* < 0.05. Missing data will be handled according to the intention-to-treat (ITT) principle, applying multiple imputation techniques when necessary to maintain statistical power and minimize bias. Access to pseudonymized datasets will be restricted to the research team, whereas access to identifiable personal information will be limited exclusively to the PI.

The sample size was estimated using G*Power version 3.1, based on a two-tailed independent samples *t*-test comparing the means between two groups (experimental and control). The following parameters were used: an effect size (Cohen’s d) of 0.58, a significance level (α) of 0.05, a statistical power (1−β) of 0.85, and an allocation ratio (N_2_/N_1_) of 1. Under these assumptions, the required sample size was 110 participants in total (55 per group) to detect a moderate effect size with 85% power and a 5% type I error rate. To account for potential attrition of 15% during the 12-week follow-up, the final recruitment target was increased to approximately 126 participants in total (63 per group).

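### Section 2.3 permits two efficacy models with no rule for choosing; with two assessments, ANCOVA on the baseline value is never less precise and should be named as the only one

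*Protocol article*

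**What the plan says.** The analysis paragraph in section 2.3 of the protocol article states: "Inferential analyses will be conducted to examine between-group and within-subject differences over time". The method follows: "using repeated-measures ANOVA or ANCOVA when appropriate, with baseline values included as covariates". No criterion is given for when one model rather than the other applies. Tests are two-sided ("All statistical tests will be two-tailed").

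The abstract fixes the number of visits: "Evaluations will be conducted at baseline and post-intervention". Each outcome measured at baseline therefore has one baseline and one post-intervention value.

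The sample size, also in section 2.3, rests on a two-sample t-test "comparing the means between two groups (experimental and control"), with "an effect size (Cohen’s d) of 0.58", "a significance level (α) of 0.05" and power 0.85, giving 55 per group. The paragraph names no outcome. It does not say whether d is scaled by the SD of the post score or of the change, and it gives no correlation between baseline and post scores.

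**The concern.** The sentence names two models that generally give different p-values on the same data, and the words meant to separate them do not. The covariate clause does not settle the matter either. In a two-visit repeated-measures ANOVA the baseline score is one of the two outcomes, so it is not obvious what entering it as a covariate as well is meant to do.

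Two things are at stake. First, precision: one of the permitted analyses uses the baseline less efficiently than the other and, under some conditions, has less power than the sample size paragraph states. Second, error control: if the choice is not fixed in advance, the more favourable result can be picked.

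**Working it through.** **Inputs from the protocol article (section 2.3 and abstract).** d = 0.58, two-sided alpha 0.05, power 0.85, 1:1 allocation, 55 per group, two assessments.

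**Assumptions, not in the document.** d is on the post-score SD; variances are equal at both visits; the baseline-to-post correlation ρ lies between 0.2 and 0.8.

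**1. The plan's own figure.** For a two-sample t-test the noncentrality is d·√(n/2). At n = 55 it is 0.58 × √27.5 = 3.04. With 108 degrees of freedom, power is 85.4%; at n = 54 it is 84.8%. The stated 55 per group is reproduced.

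**2. What each model tests with two visits.** The group-by-time test compares mean change between arms, so it is a t-test on post minus baseline. That fixes the baseline slope at 1. ANCOVA estimates the slope that minimises residual variance, so its residual variance cannot be larger, apart from the negligible cost of estimating one slope. In units of the post-score variance:

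- change score: 2(1 − ρ)
- ANCOVA: 1 − ρ²
- ratio, ANCOVA to change: (1 + ρ)/2, which is 0.65, 0.75 and 0.85 at ρ = 0.3, 0.5 and 0.7

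**3. Power at 55 per group.** Effective d is 0.58/√(2(1 − ρ)) for change and 0.58/√(1 − ρ²) for ANCOVA, with 108 and 107 degrees of freedom.

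| ρ | Effective d, change | Power, change | Effective d, ANCOVA | Power, ANCOVA |
|---|---|---|---|---|
| 0.2 | 0.459 | 66.4% | 0.592 | 86.8% |
| 0.3 | 0.490 | 72.2% | 0.608 | 88.5% |
| 0.4 | 0.530 | 78.6% | 0.633 | 90.8% |
| 0.5 | 0.580 | 85.4% | 0.670 | 93.6% |
| 0.7 | 0.749 | 97.3% | 0.812 | 98.8% |

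The change test passes 85% at ρ of about 0.49. To reach 85% it needs 76 per group at ρ = 0.3 and 66 at ρ = 0.4; ANCOVA needs 50 and 46.

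**4. If d is on the change-score SD.** The change test has 85.4% power at every ρ, by construction. ANCOVA then has effective d = 0.58 × √(2/(1 + ρ)), which is at least 0.58, so it still does no worse.

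**5. Cost of an open choice.** Null data were simulated with 55 per group and 40,000 trials per ρ. Each test alone held about 5%. Declaring significance on the smaller of the two p-values gave 7.9%, 7.8%, 7.4%, 6.8% and 6.5% at ρ = 0.2, 0.3, 0.5, 0.7 and 0.8. This does not depend on how d was scaled.

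**The case against.** Several points on the other side stand.

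- **A power shortfall is not shown.** It needs both d on the post-score SD and ρ below about 0.5, and the article states neither. A reader might infer that the trial is sized for post scores and underpowered under the ANOVA option; the sample size paragraph does not support that.
- **The two options may coincide.** If the covariate clause is taken to apply to the ANOVA as well, the group-by-time test regresses change on arm and baseline. Since post − baseline = a + b·arm + c·baseline is the same model as post = a + b·arm + (c + 1)·baseline, the estimate and p-value for arm are those of ANCOVA. That reading removes the discrepancy, but the sentence does not say that it is the one intended.
- **The analysis plan is not shown.** A fuller document may fix the choice in advance. A reader might infer that the model will be picked after the data are seen; the article does not say when it is picked. What can be reviewed is that the published wording permits both.
- **The type I error figure needs deliberate selection**, and its size is modest.

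Three stronger readings are also tempting and should not be pressed. The group main effect of a repeated-measures ANOVA would be a weak test because it averages in the baseline, but nothing in the article makes it the efficacy test. The phrase about within-subject differences may mean only the time and group-by-time terms; separate within-arm p-values are not stated, and section 2.4 makes the difference between groups the aim. In section 2.2, osteoporosis drugs are to be "considered as potential confounding variables during statistical analysis"; this is loosely put, but it commits to no particular model, and a covariate list is commonly left to the analysis plan.

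**Conclusion.** The concern holds in a limited form. Section 2.3 allows two models without a rule and gives baseline a role that is unclear when there are only two visits. In its plain form the repeated-measures option is a change-score test and is never more precise than ANCOVA.

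The size of the loss depends on ρ. With d on the post-score SD and equal variances, it is about 16 percentage points of power at ρ = 0.3 (88.5 − 72.2), 8 at 0.5 (93.6 − 85.4) and 1.5 at 0.7 (98.8 − 97.3). Under the same assumptions ANCOVA meets the stated 85% at every correlation, while the change test does so only from about 0.5 upwards. The algebra on precision and the absence of a selection rule are certain; the power loss is conditional. This is an improvement worth making, not evidence that the sample size is wrong.

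**What to change.** For every outcome measured at baseline, replace the two alternatives in section 2.3 with one efficacy analysis: ANCOVA of the post-intervention score on arm and that outcome's baseline value. State that efficacy is judged on the adjusted between-group difference with its 95% CI, and that within-group change is reported descriptively only. In the sample size paragraph, say which SD the d of 0.58 refers to.

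The cost is a change of wording. It needs no further participants, visits or data, and under the assumptions above 55 evaluable per group remains sufficient.

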### 2.4. Intervention

This study will employ a RCT design with parallel groups and a single-blind approach (evaluator blinding).

Participant allocation will be performed using computer-generated randomization. The randomization sequence will be created with the OxMaR software, a tool specifically designed for minimization and randomization in clinical trials [20]. This software will enable the random assignment of participants into two groups: a control group (CG), which will receive education on postural ergonomics techniques applied to activities of daily living, and an experimental group (EG), which will participate in Pilates Method sessions.

Each participant’s allocation number will be sealed in an opaque envelope and delivered to the researchers responsible for implementing the interventions in both the CG and EG. The evaluator conducting the outcome assessments will remain blinded to group allocation and will not have access to any information regarding participants’ assigned groups.

Following randomization and baseline assessment, the 12-week intervention period will begin. Upon completion, the same assessment battery will be re-administered to evaluate post-intervention outcomes and determine whether statistically significant differences exist between groups.

The CG will participate in two educational sessions on ergonomics and postural hygiene, each lasting 60 min and held six weeks apart. These sessions will aim to improve functional performance during activities of daily living by promoting safe movement strategies, spinal alignment, proper body mechanics, and fall prevention. This approach was designed in accordance with current clinical practice guidelines and expert recommendations on ergonomics and postural hygiene in osteoporosis management [21,22,23]. Each session will be jointly conducted by a physiotherapist and an occupational therapist with experience in osteoporosis management. Participants will receive illustrated brochures and short video demonstrations developed by the research team, based on established postural hygiene guidelines, to reinforce learning.

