## 4. Discussion

This protocol addresses an important clinical need arising from the scarcity of comprehensive non-pharmacological physical interventions targeting function, quality of life, pain, sleep, balance, and treatment satisfaction in postmenopausal women with osteoporosis. To this end, validated assessment tools, including the FIM, TUG, Functional Reach Test, VAS, PSQI, WHOQOL-BREF, QUALEFFO-41, and CSQ-8, will be employed.

Osteoporosis, due to its multidimensional nature, represents a complex condition that encompasses not only bone loss and fragility fractures but also chronic pain, fear of falling, anxiety and depressive symptoms, and limitations in daily activities. Although pharmacological treatments have proven effective in reducing fracture risk, the associated psychosocial deterioration often compromises patients’ autonomy and quality of life [2,3,4,6].

In this context, the Pilates Method emerges as a promising approach to address these multifaceted challenges, emphasizing postural control, core activation, breathing, and low-impact movement [12,13,14]. Pilates may exert its beneficial effects through multiple mechanisms.

First, it improves balance and postural control by activating trunk-stabilizing muscles and promoting proper body alignment, potentially enhancing performance in balance-related tests such as the Functional Reach Test and TUG [11,17]. Second, it strengthens muscles and increases endurance, leading to improved motor performance and functional independence [3,4]. Moreover, Pilates may help reduce chronic pain by improving postural alignment, redistributing mechanical loads, and incorporating breathing and body-awareness techniques [9,11,16]. It has also been associated with better sleep quality and psychological well-being, as supervised low-impact exercise can reduce anxiety and fear of falling [5,8]. Notably, Aibar-Almazán et al. [9] reported that a Pilates program improved sleep quality, depression, and anxiety in postmenopausal women. Furthermore, reductions in kinesiophobia, pain, and functional limitations have been observed following Pilates interventions, reinforcing participants’ perception of safety in movement and their overall quality of life, thereby supporting Pilates as a safe and effective form of exercise [16].

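### No primary outcome is named among seven efficacy instruments all tested at an unadjusted 0.05, so the stated 5% type I error and 85% power belong to no identified efficacy conclusion

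*Protocol article*

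**What the plan says.** The Discussion (Section 4) gives the full battery, "including the FIM, TUG, Functional Reach Test, VAS, PSQI, WHOQOL-BREF, QUALEFFO-41, and CSQ-8, will be employed". The Abstract and Sections 2.5.2 and 2.5.3 list the same eight instruments. None of these places ranks them as primary or secondary. Section 4 later gives priority to function, pain and quality of life, which is still several outcomes.

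On testing, Section 2.3 states that "Inferential analyses will be conducted to examine between-group and within-subject differences over time", by repeated-measures ANOVA or ANCOVA, and adds: "All statistical tests will be two-tailed, with the significance level set at" p < 0.05. Section 2.4 has the whole battery repeated after the intervention to "determine whether statistically significant differences exist between groups".

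On size, Section 2.3 takes a two-sided two-sample t-test with d = 0.58 and arrives at 55 per group "to detect a moderate effect size with 85% power and a 5% type I error rate". It names no instrument, difference or standard deviation.

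The Abstract's hypothesis covers four areas at once: "It is hypothesized that Pilates will produce clinically meaningful improvements in balance, pain, sleep quality, and health-related quality of life". No rule says how many must succeed. The Abstract also describes the analysis as descriptive and the effects as preliminary, ahead of a later definitive trial.

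**The concern.** A type I error rate and a power are properties of a defined test leading to a defined conclusion. Here the test used for sizing has no outcome, and the analysis offers at least seven outcomes on which efficacy could be declared. Nothing in the text stops a single significant instrument from becoming the efficacy result, chosen after the data are known. The error rate of that conclusion would exceed 5%, and a reader of the final report could not tell which outcome the trial had been sized to answer.

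This is more than detail left to a statistical analysis plan. The protocol itself fixes the significance level, the sample size and the hypothesis. Only the outcome that would connect them is absent.

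**Working it through.** **Inputs from the protocol.** d = 0.58, two-sided alpha 0.05, power 0.85, 1:1 allocation, 55 per group (Section 2.3). Eight instruments (Sections 2.5.2, 2.5.3 and 4). CSQ-8 measures satisfaction with care, and satisfaction is in neither the objective nor the hypothesis, so the efficacy family is seven: FIM, TUG, FRT, VAS, PSQI, WHOQOL-BREF and QUALEFFO-41.

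**Assumptions.** One between-group test per instrument. The correlation between instruments is not given, so a range is shown.

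**1. The plan's own figure.** The noncentrality is d × √(n/2) = 0.58 × √(55/2) = 3.04, with 108 degrees of freedom. The noncentral t distribution gives power of 85.4% at 55 per group. Solving for 85% gives n = 54.36, so 55 per group and 110 in total. The stated figure reproduces, for one comparison.

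**2. Chance of at least one p < 0.05 if Pilates affects none of the seven outcomes.**
- Independent tests: 1 − 0.95^7 = 0.302.
- Correlated tests: two-sided z-tests with Z_j = √r·Z_0 + √(1 − r)·e_j, 400,000 simulated draws.

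| Assumed common correlation | Any significant result | Significant and favouring Pilates |
|---|---|---|
| 0 | 30.2% | 16.3% |
| 0.3 | 27.1% | 13.7% |
| 0.5 | 22.9% | 11.5% |
| 0.7 | 17.8% | 8.9% |
| 0.9 | 11.4% | 5.7% |

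For a two-sided 5% test of one outcome, the corresponding values are 5% and 2.5%. Every row exceeds them.

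**3. What each remedy does to the design.**
- One primary outcome at two-sided 0.05: type I error 5%, and power 85.4% at 55 per group if d = 0.58 holds for that outcome. The sample size is unchanged.
- All seven kept co-equal with Bonferroni: alpha = 0.05/7 = 0.00714. Power per outcome at 55 per group falls to 61.8%. Regaining 85% takes 85 per group, that is 170 evaluable, or 170/(1 − 0.15) = 200 recruited at the plan's 15% attrition.

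**The case against.** The strongest reply is that the sample-size paragraph is correct as a statement about one comparison, that multiplicity procedures are commonly left to an analysis plan not shown here, and that the Abstract presents the work as preliminary and descriptive. The first part stands: the arithmetic is right, and the fault is that the comparison is unidentified. The second stands for the choice of procedure, since the absence of Holm or a fixed sequence would be no finding by itself. It does not cover an absent primary outcome when the protocol has already set the alpha and the sample size. The third does not rescue the plan. Sections 2.3 and 2.4 prescribe significance tests, the trial is sized at 85% power, and Section 5 describes it as designed to evaluate efficacy. Section 2.3 also promises effect sizes with 95% confidence intervals, which helps interpretation but does not replace a decision rule.

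A reader might infer more than the text supports:
- **That a false efficacy claim is likely.** The calculated risk stays below even odds and applies only if there is no effect on any outcome. It passes 50% only at about 15 independent tests (1 − 0.95^15 = 0.537), for example if every quality-of-life domain were tested. The protocol describes the domains but does not say that they will be tested.
- **That all eight instruments belong to the efficacy family.** A significant CSQ-8 result would say something about satisfaction, not efficacy.
- **That power is far below 85% because all four hypothesised areas must succeed.** No such rule is stated. Balance and quality of life each have two instruments, so a calculation with one test per area would not match the plan either.
- **That evaluator blinding fully protects the functional measures.** Section 2.5.2 has FIM scored partly by interview with participants who know their group, so its protection is partial.

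**Conclusion.** The point holds in a limited form. No primary outcome is designated, every test uses an unadjusted two-sided 0.05, and the sample-size calculation is attached to no named outcome. The 5% and 85% are right for a single t-test but apply to no identified efficacy conclusion. Under no effect on any outcome, the chance of at least one significant result over the seven efficacy instruments is about 11% to 30%, roughly two to six times the nominal 5%. That range rests on one test per instrument and on assumed common correlations from 0.9 down to 0. The descriptive wording in the Abstract is a further inconsistency to resolve. It is worth correcting because the remedy costs little now and would not be credible once results by group are known.

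**What to change.** Before any unblinded data are seen:
1. Name one primary outcome, measured at the post-intervention assessment and tested at two-sided 0.05. State the time point unambiguously: Section 2.5 puts the second assessment after two months, while the intervention lasts 12 weeks, and these passages must be reconciled.
2. Tie d = 0.58 to that outcome as a difference and standard deviation in its own units. If 0.58 is not defensible for it, restate the power.
3. State that the efficacy conclusion rests on that outcome.
4. Make all other outcomes secondary, either adjusted for multiplicity (for example by Holm) or reported as estimates with 95% confidence intervals and no confirmatory claim.
5. Bring the Abstract's description of the analysis into line with Section 2.3.

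The choice of outcome is the investigators'. One measured by the blinded evaluator would be less exposed to expectation bias, a risk that Section 4 acknowledges because of the unequal contact time.

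The cost is wording in the protocol and the registration, with no extra participants if 0.58 holds for the chosen outcome. The small downside is that an isolated significant secondary result can no longer be the headline.
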